### Quality control and data management

This is a 20-week clinical trial, in which participants need to take herbal medicine and acupuncture for 8 weeks, and accept a 12-week follow-up, attend four assessment visits (rehabilitation evaluation), obtain one set of laboratory tests (safety assessments). Before the study, the trial protocol has been reviewed and revised by experts on acupuncture, neurology, rehabilitation, statistics and methodology several times. All the members belonging to the trial are asked to take part in a series of training to ensure that the personnel involved fully understand the research protocol and standard operating procedures for the study. During the study, the Clinical Research Institute of Zhejiang Provincial is responsible for generating the allocation sequence, quality control, and censors make regular visits (once a month) to monitor for protocol violations, the recruitment rate, AEs and participant compliance. This clinical trial is independent from sponsors and competing interests. The clinical coordinators of three centres are specifically designated to enrol participants and assign participants to interventions, but not to participate in treatment and assessment for participants. Outcome assessors and data analysts will be blinded after assignment to interventions, without access to patients’ group information.

The measurements are mainly rehabilitation evaluations. All of the data will first be recorded on the paper version of the case report form by assessors, then double entered into the EDC system electronically. A specified statistics centre of the Clinical Research Institute of Zhejiang Province will be responsible for data management. All data will be double entered to ensure accuracy. The source of any inconsistencies will be explored and resolved.

### Sample size calculation

The primary efficacy parameter is the change in MBI scores from baseline to the end of treatment after 8 weeks. Sample size calculations are based on our preliminary test and previous study.^21^
^22^ The expected difference between CR group and IMR group is a 10 value, that is to say the score of MBI of the IMR group was a 10 value higher than that of the CR group, and the SD is about 31. A two sided 5% significance level and 80% power were considered, and the following equation was used:
[figure not shown]

Approximately 150 participants in each group were calculated to be required. Estimating a 20% dropout rate, each group will require 180 initial participants.

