**Methods and analysis:**

360 participants recruited from three large Chinese medical hospitals in Zhejiang Province will be randomly divided into the integrative medicine rehabilitation (IMR) group and the conventional rehabilitation (CR) group in a 1:1 ratio. Participants in the IMR group will receive acupuncture and Chinese herbs in addition to basic Western medicine and rehabilitation treatment. The CR group will not receive acupuncture and Chinese herbal medicine. The assessment data will be collected at baseline, 4 and 8 weeks postrandomisation, and then at 12 weeks’ follow-up. The primary outcome is measured by the Modified Barthel Index. The secondary outcomes are the National Institutes of Health Stroke Scale (NIHSS), Fugl-Meyer Assessment, the mini-mental state examination and Montreal Cognitive, Hamilton's Depression Scale and Self-Rating Depression Scale, and the incidence of adverse events.

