### Statistical analysis

Efficacy and safety analyses will be conducted according to the intention-to-treat (ITT) principle by a statistician blinded to group allocation. Missing values will be imputed by the last-observation-carried-forward method. All statistical analyses will be performed using Statistical Product and Service Solutions (SPSS) statistical package program (V.17.0, SPSS Inc, Chicago, Illinois, USA). The primary outcomes (MBI) and FMA will undergo ITT analysis including all the patients who are randomised. The analysis of cognitive impairment and emotional disorder will be made among the defined population of corresponding dysfunction. Continuous variables will be expressed as means with SDs. For normally distributed variables, two independent samples will be compared by independent sample t test. On the other hand, for abnormally distributed variables, non-parametric tests will be used and the data will be expressed as medians with ranges. A p value of less than 0.05 is considered as statistical significance. Safety analysis is based on the frequency of AEs relating to the treatment.

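### The 20% dropout allowance is multiplied on (150 × 1.2 = 180) instead of divided out (150 / 0.8 = 188), so 180 per group leaves 144 completers, not the required 150

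*Protocol article*

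**What the plan says.** The Sample size calculation section of the protocol article defines the endpoint: "The primary efficacy parameter is the change in MBI scores from baseline to the end of treatment after 8 weeks". The planning inputs follow: "The expected difference between CR group and IMR group is a 10 value", "the SD is about 31", and "A two sided 5% significance level and 80% power were considered". From these the section derives roughly 150 participants per group. The dropout step comes next: "Estimating a 20% dropout rate, each group will require 180 initial participants".

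The Abstract (Methods and analysis) carries the result forward as the size of the trial: "360 participants recruited from three large Chinese medical hospitals in Zhejiang Province will be randomly divided", with allocation to the integrative medicine group and "the conventional rehabilitation (CR) group in a 1:1 ratio".

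The Statistical analysis section says that the primary outcome is analysed by intention to treat in everyone randomised. It also says: "Missing values will be imputed by the last-observation-carried-forward method".

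**The concern.** A dropout rate is a fraction of the patients who start. If 20% of the starters are lost, 80% remain, so the number to enrol is the number needed divided by 0.8. The plan has added 20% of the number needed instead. It therefore states a requirement (about 150 per group) and a dropout rate (20%) that its enrolment figure does not satisfy together.

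What is at stake is the stated justification for 360 patients. The error can be checked from two adjacent sentences, and a reader who relies on the stated 20% tolerance would be relying on a margin that is smaller than claimed.

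**Working it through.** **Inputs**, all from the Sample size calculation section: difference 10 points, SD 31, two-sided alpha 0.05, power 80%, dropout 20%. The 1:1 allocation is from the Abstract.

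**Step 1: the base figure reproduces.** The sample size equation is not shown in the text, so the standard two-means formula is used:

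n = 2 × [(1.960 + 0.842) × 31 / 10]² = 150.9 per group, so 151.

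The t-test version gives 151.8, so 152. A stated figure of about 150 is fine.

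**Step 2: the dropout step.**

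| Rule | Calculation | Per group | Total |
|---|---|---|---|
| Plan's figure | 150 × 1.2 | 180 | 360 |
| Division by the retained fraction | 150 / 0.8 = 187.5 | 188 | 376 |
| Same, from 151 | 151 / 0.8 = 188.75 | 189 | 378 |

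Multiplication matches the plan exactly. Relative to division from 150, the plan is 8 per group (16 in total) short.

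**Step 3: what 180 delivers.** Completers at 20% loss: 180 × 0.8 = 144, which is 150 − 144 = 6 short. The dropout rate at which 150 remain: 1 − 150/180 = 16.7%.

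**Step 4: power in completers only** (two-sample t-test, difference 10, SD 31):

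| n per group | Power |
|---|---|
| 144 | 77.9% |
| 150 | 79.5% |
| 152 | 80.0% |

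The loss attributable to the dropout step is 79.5 − 77.9 = 1.6 percentage points. The normal formula gives 78.1% at 144 and 79.8% at 150.

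**Step 5: power in the planned analysis.** With last observation carried forward, 180 per group are analysed. Let *f* be the share of the 10-point difference that dropouts carry forward on average. The documents give no value for *f*, so it is an assumption and is shown over its range from 0 to 1. The SD is held at 31. Expected difference = 0.8 × 10 + 0.2 × 10*f* = 8 + 2*f*.

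| *f* | Expected difference | Power, n = 180 |
|---|---|---|
| 1 | 10.0 | 86% |
| 0.75 | 9.5 | 83% |
| 0.59 | 9.18 | 80% |
| 0.5 | 9.0 | 78% |
| 0 | 8.0 | about 69% |

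The break-even is (9.18 − 8) / 2 = 0.59. Dropouts must carry forward about 59% of the effect for power to reach 80%.

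The assessment schedule (baseline, week 4, week 8) shows why *f* can fall anywhere in this range. A patient lost before week 4 has only the baseline value to carry, so the change is zero. A patient lost after week 4 carries the week-4 change.

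**The case against.** The strongest reply is that 144 is not the number the plan analyses. The Statistical analysis section includes all randomised patients and fills gaps by carrying values forward. On 180 per group, with the difference of 10 and SD of 31 intact, power is 86%. This stands as far as power is concerned. A reader might infer from the dropout slip that 360 patients cannot deliver 80% power. The documents do not support that for the planned analysis: the answer depends on *f*, on which they are silent, and the SD could also change once some change scores are set to zero. Equally, 86% is not secure, since it needs the full difference to survive imputation.

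The reply does not rescue the dropout step itself. An allowance is added because dropouts are expected to cost information. On that reasoning the allowance must leave 150, and it leaves 144.

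Two further points stand. First, the plan does not say whether 20% is the loss by week 8, when the primary endpoint is measured, or over the whole 20-week trial. If it is the latter, fewer may be lost by week 8. At 15% loss, 180 × 0.85 = 153 completers remain and completer power is 80.3%. Second, the inputs are approximate. With 144 completers, the normal formula gives 79.4% at SD 30.5 and 76.8% at SD 31.5, a spread as large as the effect of the slip.

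One might also read the 20% as a simple uplift on 150. The text calls it a dropout rate and applies it to the patients at the start, so that reading does not fit the wording.

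**Conclusion.** The dropout inflation is wrong as written: 180 per group should be 188 on the plan's own inputs (376 in total against 360). This needs no assumption beyond reading a 20% dropout rate as a share of those enrolled.

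The consequence is minor. Taking all 20% as lost before week 8, a completers-only comparison has about 78% power, and the plan's true tolerance for keeping 150 is 16.7%. For the planned intention-to-treat analysis with carried-forward values, power at SD 31 lies between about 69% and 86%. It may be above or below the target, and a shortfall is not shown.

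**What to change.** Keep 360 and correct the sentence in the Sample size calculation section. Either of these would do:

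- *180 per group leaves 144 completers at 20% dropout, giving about 78% power in a completers-only comparison.*
- *180 per group tolerates 16.7% dropout while retaining about 150 per group.*

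It would help to add whether the dropout rate refers to week 8 or to the end of follow-up.

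The cost is one sentence and a slightly less favourable stated margin. No extra patients are needed. Since the Participant recruitment section gives recruitment as closing on 31 December 2014, restating the justification is more proportionate than enlarging the trial by 16.

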### Statistical analysis

Efficacy and safety analyses will be conducted according to the intention-to-treat (ITT) principle by a statistician blinded to group allocation. Missing values will be imputed by the last-observation-carried-forward method. All statistical analyses will be performed using Statistical Product and Service Solutions (SPSS) statistical package program (V.17.0, SPSS Inc, Chicago, Illinois, USA). The primary outcomes (MBI) and FMA will undergo ITT analysis including all the patients who are randomised. The analysis of cognitive impairment and emotional disorder will be made among the defined population of corresponding dysfunction. Continuous variables will be expressed as means with SDs. For normally distributed variables, two independent samples will be compared by independent sample t test. On the other hand, for abnormally distributed variables, non-parametric tests will be used and the data will be expressed as medians with ranges. A p value of less than 0.05 is considered as statistical significance. Safety analysis is based on the frequency of AEs relating to the treatment.

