## Introduction

Stroke is the second most common cause of death and leading cause of adult disability worldwide.^1^ The number of patients who die from stroke is more than three times that of those who die from coronary heart disease.^2^ Modern Western medicine in China undoubtedly occupies the dominant position in prevention and treatment of stroke. However, most patients with stroke are treated with one or more types of traditional Chinese medicine (TCM) in addition to Western medicine. The role of TCM should not be ignored.^3–5^ With the development of integrative medicine (IM), which was established in the 1980s, more and more patients with stroke receive IM treatment. The main integrative treatment includes the standard Western medicine and rehabilitation for stroke, as well as acupuncture and (or) Chinese herbs.^6^ Nevertheless, there is not yet enough evidence to show the effect of IM for stroke. More rigorously designed, large scale, multicentre randomised trials are necessary to assess the effectiveness of IM on stroke rehabilitation.^7^

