### Randomisation and blinding

Randomisation was performed on Excel computer software for the study. The generated list of random numbers was printed, cut into small pieces, separated and placed into sequentially numbered, opaque, sealed envelopes. The envelopes were saved by special screeners. When a participant was included, the screeners opened the envelope to get the group information. Then the subject was informed whether they would be in the treatment group or control group, with or without acupuncture and Chinese herbs. All of the rehabilitation therapists, outcome assessors and data analysts are blinded to group assignments. However, it is impossible to make acupuncturists blinded, because they are trained to perform the treatment for participants of the IMR group.

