### Conventional rehabilitation group

Patients in the CR group do not receive acupuncture and Chinese herbs. This group only receives basic Western medical and rehabilitation treatment, in the same frequency, with the same course of treatment as the IMR group.

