### The incidence of adverse events

Participants are to be questioned and report all adverse events (AEs) at each visit point, and all AEs reports will be recorded and assessed by the investigators. If serious AEs occur, the researchers should report to the principal investigator and ethics committee immediately, who will make a decision on whether or not the participant needs to withdraw from the study. If the participant suffered serious AEs, unbinding is permissible and procedure is followed for revealing a participant's allocated intervention during the trial. Compensation will be provided to those who suffer harm from trial participation.

In order to assess the safety of herbal medicine, we will perform the following tests on participants of the IMR group at baseline (week 0) and after treatment (week 12): routine blood test, routine urine test, routine faeces test, kidney function test and liver function test. In addition, investigators will ask subjects at each visit whether they have experienced allergies or gastrointestinal discomfort during the study period.

The AEs of acupuncture may include local bleeding, haematoma, pallor, sweating or dizziness, fainting during the acupuncture treatment, unbearable prickling or retained needle after treatment. The investigator should record the date of occurrence, time, degree, measurement related to the treatment and consequence.

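### Safety is to be analysed by intention to treat only, so any non-start or crossover would understate treatment-related harm; an analysis by treatment received should be added

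*Protocol article*

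**What the plan says.** The Statistical analysis section of the protocol article puts efficacy and safety under one rule: "Efficacy and safety analyses will be conducted according to the intention-to-treat (ITT) principle". For the Modified Barthel Index and the Fugl-Meyer Assessment it adds that they "will undergo ITT analysis including all the patients who are randomised". It closes with "Safety analysis is based on the frequency of AEs relating to the treatment". That sentence fixes which events are counted. It does not say who forms the denominator, or under which arm a participant is counted, so the intention-to-treat rule still governs both.

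The treatments whose harms are at issue belong to one arm. Under Conventional rehabilitation group: "Patients in the CR group do not receive acupuncture and Chinese herbs". The acupuncture events to be watched for are listed under The incidence of adverse events: "local bleeding, haematoma, pallor, sweating or dizziness, fainting during the acupuncture treatment, unbearable prickling or retained needle after treatment". The same section asks about allergy and gastrointestinal complaints at each visit, and plans safety laboratory tests for the IMR group.

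Allocation is open to participants. Under Randomisation and blinding: "Then the subject was informed whether they would be in the treatment group or control group, with or without acupuncture and Chinese herbs".

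**The concern.** Intention to treat counts every participant under the assigned arm, whatever was received. An IMR participant who never starts acupuncture or herbs adds to the IMR denominator without being at risk of harm from them. A CR participant who obtains either brings any resulting event into the CR arm. Both departures pull the two arms together.

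For efficacy this is usually accepted as conservative. For safety it works the other way: it favours a finding of little or no added harm. The article states this choice outright, so it is not a detail left to a fuller document, and an analysis plan that followed it would carry the problem forward.

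Departures are conceivable on the article's own account. Participants know their arm, the sites are Chinese medical hospitals, and the Introduction says that "most patients with stroke are treated with one or more types of traditional Chinese medicine (TCM) in addition to Western medicine". Study treatment lasts 8 weeks, but AEs are asked about at every visit, including the one 12 weeks after treatment ends. CR participants could obtain acupuncture or herbs in that interval.

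**Working it through.** **Inputs from the article.** 360 participants allocated 1:1, so 180 per arm; safety analysed by assigned arm; acupuncture and herbs given in the IMR arm only.

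**Inputs the article does not give.** AE risk with and without exposure, the share of IMR never starting, and the share of CR exposed. All values for these below are assumptions.

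**The plan's own figure.** The only design calculation is for the Modified Barthel Index (difference 10, SD 31, two-sided 5%, 80% power). It gives 2 × (1.960 + 0.842)² × 31² / 10² ≈ 150.9, so 151 per group, against about 150 stated. It reproduces, and nothing below depends on it.

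**Formula.** Let p₁ be the AE risk if exposed and p₀ the risk if not, n the share of IMR never exposed, and c the share of CR exposed. Assume that p₁ and p₀ are the same for those who depart from their assignment as for everyone else.

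- As-randomised IMR risk: (1 − n)p₁ + n p₀
- As-randomised CR risk: (1 − c)p₀ + c p₁
- Difference: (1 − n − c)(p₁ − p₀)

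The retained share, 1 − n − c, does not depend on the AE risks.

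**Numbers**, with p₁ = 10% and p₀ = 2% (difference by exposure: 8.0 points):

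| n | c | IMR | CR | Difference | Share kept | Power, 180 per arm |
|---|---|---|---|---|---|---|
| 0 | 0 | 10.0% | 2.0% | 8.0 points | 100% | 0.90 |
| 5% | 5% | 9.6% | 2.4% | 7.2 points | 90% | 0.82 |
| 10% | 10% | 9.2% | 2.8% | 6.4 points | 80% | 0.73 |
| 20% | 10% | 8.4% | 2.8% | 5.6 points | 70% | 0.64 |

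For the second row: 0.95 × 10% + 0.05 × 2% = 9.6%; 0.95 × 2% + 0.05 × 10% = 2.4%; difference 7.2 points.

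If instead the event cannot occur without exposure (p₁ = 10%, p₀ = 0), the differences are 10.0, 9.0, 8.0 and 7.0 points. The shares kept are identical, and power falls only from 0.99 to 0.98, 0.94 and 0.90. The loss of power therefore depends on the assumed risks; the proportional shrinkage does not.

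**The case against.** The strongest reply is that nothing in the article shows departures will be common, and several provisions work against them. The Exclusion criteria remove, before randomisation, patients who cannot accept acupuncture or Chinese medicine. Under Interventions and comparison, both are delivered during the inpatient stay. The CR group is defined as receiving neither. Quality control and data management provides monthly visits that check protocol violations and compliance. All of this stands. It makes large departures unlikely, without ruling out later refusal or use by CR participants during follow-up.

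It can also be said that AEs are to be recorded by their relation to treatment, so a needle haematoma in a CR participant would be seen for what it is. That also stands, but it does not decide the denominator or the arm. Finally, an as-randomised AE comparison is legitimate and protected by randomisation, and no safety hypothesis or margin is planned. That is a reason to keep the comparison, not to make it the only one.

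Three stronger readings are tempting, and the article does not support them.

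- A reader might infer that harms will certainly be diluted, perhaps by 40%. That figure needs n = c = 20%, for which there is no source. The planned 20% dropout is not a non-start rate, because the article does not say when participants would leave.
- A reader might take the Introduction's remark on use of traditional Chinese medicine as evidence of crossover. It describes stroke care in general, not this trial's CR inpatients.
- A reader might assume that every listed acupuncture event requires a needle. Pallor, sweating and dizziness do not, and allergy and gastrointestinal complaints also have a background rate. This is why the main table uses a non-zero unexposed risk.

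**Conclusion.** The point holds as a conditional one. The article prescribes intention to treat for safety and states no analysis by treatment received. If there is non-start or crossover, and if the treatment raises AE risk, the as-randomised risk difference is too small by the factor (1 − n − c).

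The direction follows from the formula, given equal risks for those who depart. The size cannot be derived from the article. Under assumed rates, 5% in each arm keeps 90% of the difference and 10% in each arm keeps 80%; with no departures there is no effect. The trial's own safeguards probably put it at the small end. The change is still worth making, because the error would run in the unsafe direction and the correction is cheap.

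**What to change.** In the Statistical analysis section, limit the intention-to-treat statement to efficacy and define a safety set analysed by treatment actually received:

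- acupuncture AEs among participants with at least one acupuncture session;
- herb AEs among participants with at least one herbal dose;
- CR participants who received either one classed as exposed to it.

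Keep the as-randomised AE table alongside.

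The cost is a revised sentence or two, one more table, and an exposure item recorded at the existing visits in both arms, follow-up included. Sample size and treatment are unaffected.

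There are two limitations to state with the results. The treatment-received comparison is not protected by randomisation, which is the reason for keeping both tables. And because safety laboratory tests are planned for the IMR group only, CR participants who cross over would contribute reported AEs but no laboratory results; an exposure item does not fill that gap.

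### LOCF, the only missing-data method the article states, can bias the week-8 MBI difference in a population that is still recovering

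*Protocol article*

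**What the plan says.** All of this is in the protocol article.

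- **Method for missing data** (Statistical analysis): "Missing values will be imputed by the last-observation-carried-forward method". No other method is stated.
- **Analysis set** (same section): "The primary outcomes (MBI) and FMA will undergo ITT analysis including all the patients who are randomised".
- **Test** (same section): for normally distributed variables, "two independent samples will be compared by independent sample t test"; otherwise a non-parametric test.
- **Endpoint** (Sample size calculation): "The primary efficacy parameter is the change in MBI scores from baseline to the end of treatment after 8 weeks".
- **Planning values** (same section): "The expected difference between CR group and IMR group is a 10 value", "the SD is about 31", two-sided 5% level, 80% power. This gives about 150 per group, raised to 180 after "Estimating a 20% dropout rate".
- **Visits** (Outcome assessment): baseline, weeks 4 and 8, and 12 weeks after the end of treatment.
- **Population and care** (Inclusion criteria; Interventions and comparison): ischaemic stroke 30–40 days earlier; both arms have rehabilitation 2 h a day, 6 days a week.
- **Allocation** (Randomisation and blinding): participants are told their group.

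**The concern.** LOCF is unbiased for a mean only if patients would not have changed, on average, after their last visit. Here change is the endpoint, and both arms are treated in order to produce it. A patient lost before week 4 is scored as having gained nothing. A patient lost between weeks 4 and 8 keeps the week-4 gain.

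Two consequences follow. If IMR works, the part of its advantage that builds up after a patient leaves is lost, and the estimated difference shrinks. If the arms lose patients at different rates, the arm that loses more is held back more, and a difference in retention is read as a difference in efficacy. Unequal loss is plausible because participants know their allocation: controls had to be able to accept acupuncture and herbs but do not receive them, and IMR patients carry an extra daily treatment.

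What is at stake is the single primary estimate and, if dropout differs by arm, its type I error.

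**Working it through.** **1. The plan's own figure.** n per arm = 2 × [31 × (1.960 + 0.842) / 10]² = 150.9, which agrees with the stated figure of about 150. The 180 is 150 × 1.2. At 20% loss, up to 180 × 0.2 = 36 values per arm are imputed and 144 observed.

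**2. Inputs the article does not give (assumptions).** Mean CR gain of 12 points at week 4 and 22 at week 8. With a true effect, IMR gains 5 and 10 points more (17 and 32). Of the patients lost before week 8, half leave before week 4, and leaving is unrelated to outcome within an arm. The article does not say when in the 20 weeks its 20% dropout occurs, so each case is computed twice: all of it before week 8, and half of it after.

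**3. Formula.** With d the proportion of an arm lost before week 8:

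LOCF mean change = (1 − d) × gain at week 8 + (d/2) × gain at week 4 + (d/2) × 0.

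Taking 31 as the SD of the change, SE = 31 × √(2/180) = 3.27. Rejection rates use the normal approximation.

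**4. Equal dropout, true difference 10.**
- All before week 8 (d = 0.20): IMR 0.80 × 32 + 0.10 × 17 = 27.3; CR 0.80 × 22 + 0.10 × 12 = 18.8; difference **8.5**.
- Half after week 8 (d = 0.10): IMR 0.90 × 32 + 0.05 × 17 = 29.65; CR 0.90 × 22 + 0.05 × 12 = 20.4; difference **9.25**.

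**5. Equal dropout, no true difference.** Both arms have the same mean, so the difference is **0** and the type I error stays at about 5%.

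**6. Dropout 25% CR, 15% IMR, no true difference.**
- All before week 8: IMR 0.85 × 22 + 0.075 × 12 = 19.6; CR 0.75 × 22 + 0.125 × 12 = 18.0; spurious difference **+1.6**. 1.6 / 3.27 = 0.49, and the two-sided rejection rate is **7.8%**.
- Half after week 8 (12.5% and 7.5%): IMR 0.925 × 22 + 0.0375 × 12 = 20.8; CR 0.875 × 22 + 0.0625 × 12 = 20.0; spurious difference **+0.8**, rejection rate **5.7%**.

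**7. Rates reversed (25% IMR, 15% CR).** With no effect the spurious difference is −1.6 or −0.8. With a true difference of 10 and all dropout before week 8: IMR 0.75 × 32 + 0.125 × 17 = 26.1; CR 19.6; difference 6.5.

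**8. Other assumptions.** With CR gains from 10 to 30 points, all loss before week 8 and every dropout carried either at baseline or at half of the week-8 gain, equal 20% dropout turns 10 into 8.0 or 9.0. In simulations at a CR gain of 20 with no effect (4,000 trials, 180 per arm), the type I error was about 6% to 9% at 15% IMR v 25% CR, and about 10% to 26% at the more extreme 10% v 30%.

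**9. Standard error.** In the same simulations, with equal 20% dropout, a true difference of 10 and baseline carried, the mean reported SE was 3.11 and the actual sampling SD of the LOCF estimate was 3.13. The t test's SE is therefore about right for what LOCF estimates. What is overstated is the information: an analysis of the 144 observed values per arm has SE 31 × √(2/144) = 3.65.

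**The case against.** The best defence is that the bias is conditional. With equal dropout and no effect there is none. With equal dropout and a real effect the estimate shrinks, which is conservative for a superiority claim. The article gives one dropout figure with no split by arm and does not tie it to week 8. Treatment is given during the inpatient stay, so much of the loss may come after the primary endpoint. All of this stands. It is why the sizes are given as ranges and why the claim is that LOCF can bias the result, not that it will.

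The defence does not rescue LOCF as the primary method. Whether dropout is balanced and late is unknown in advance, and the stated method is valid for the size of the effect only if it is close to nil before week 8 or if recovery has stopped.

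A reader might infer three stronger points that the documents do not support.

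- **That the SE is understated and the confidence interval too narrow.** Step 9 shows otherwise. The interval has about the right width for the LOCF estimate; the fault is where it is centred.
- **That withdrawal after a serious adverse event contradicts ITT.** The adverse events section refers such cases to the principal investigator and the ethics committee, "who will make a decision on whether or not the participant needs to withdraw from the study". The Statistical analysis section still analyses every randomised patient for MBI and imputes what is missing, so the two are compatible.
- **That a rule for deaths and sensitivity analyses are missing from the plan.** These are commonly left to the SAP, which is not shown. For the same reason, LOCF can be called the only stated method of this article and no more.

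**Conclusion.** The point holds in a conditional form. The article fixes LOCF for a week-8 change endpoint in patients expected to improve, with 20% dropout planned and only baseline or week 4 to carry forward. Under the assumed gains, a true difference of 10 is estimated as about 8.5 to 9.25 when dropout is equal. At 25% CR v 15% IMR a null effect appears as about +0.8 to +1.6, with type I error about 5.7% to 7.8% at SD 31; the sign follows whichever arm loses more patients. The ranges reflect how much of the dropout precedes week 8. They rest on a recovery curve, a dropout split and a dropout timing that the article does not give, and they grow under more extreme imbalance. In addition, up to about 36 imputed values per arm are treated as observed, which overstates the information available without making the t-test SE wrong for the LOCF estimator.

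**What to change.** In the Statistical analysis section, replace LOCF as the primary method with one that is valid under missing at random: a mixed model for repeated measures on all observed MBI values, with baseline MBI, centre, treatment, visit and treatment-by-visit interaction, testing the treatment contrast at week 8. Keep LOCF only as a sensitivity analysis, preferably beside one that allows data to be missing not at random.

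One detail needs a sentence. With baseline as a covariate, a patient who has no MBI after baseline contributes nothing to this model. To honour the commitment to all randomised patients literally, model baseline as one of the repeated outcomes, or use multiple imputation.

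The cost is a reworded paragraph and modest extra analysis. The visits and MBI values are already scheduled. The change should be fixed before anyone sees outcomes by group.
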